Following the training, we estimate that adequate knowledge and skills will have been provided to the participating PTs, enabling them to deliver the intervention to their patients based on the principles of the PDDM model. For each of their patients, the PT will have to provide clinical data based on their use of the PDDM model to guide their assessment and interventions over a 6-weeks period (or less if the patient is discharged before the end of the 6-week period). The data collected relates to the selected outcomes to measure feasibility, acceptability and preliminary effect of the intervention. Concerning the specific use of the PDDM model in order to guide the clinicians’ assessment and treatment approach, an electronic tool using Excel will be developed by the research team. This tool aims to foster the identification by the clinicians of the relative contribution of each domain to the patient health condition by creating a complete personalized profile and to gather baseline patients’ sociodemographic characteristics. This tool will be presented to the PTs during the training seminar.

**Outcomes**

The primary outcomes measures will assess feasibility of implementation, clinician’s acceptability and patient’s satisfaction of the intervention. These outcomes will be measured at T0 (i.e., before the workshop), T1 (i.e., after the workshop), T2 (i.e., at patient’s initial visit/enrollment) and T3 (i.e., after follow-up period) (see Figure 1). Sekhon et al. defined acceptability as a “multi-faceted construct that reflects the extent to which people delivering or receiving a healthcare intervention consider it to be appropriate” [18]. It includes several constructs such as attitude towards the intervention, the intervention’s burden and ethicality for the individual, the intervention coherence, perceived effectiveness and self-efficacy in performing the intervention. Feasibility refers to the assessment of whether or not it will be feasible to conduct an intervention in a particular setting and includes issues such as willingness of individuals to participate in the study, the adherence/compliance of participants to the intervention (ex : response rate to questionnaire, loss to follow up) and whether the intervention can be delivered as intended within the clinical setting [19]. Despite the fact that there is some overlap between these constructs, we decided to use specific data collection procedures for each aspect included in these constructs.

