**Objectives**

The general objective of this project is to assess the feasibility of conducting a complete RCT to evaluate the impact of the PDDM model on improving the management of non-specific LBP. The specific objectives are:

- To evaluate the feasibility of the PDDM to guide assessment and treatment;
- To document the clinicians’ acceptability and patient satisfaction of its use in clinical settings;
- To explore the model’s short-term effect on patient’s clinical outcomes (gather preliminary evidence of change in levels of pain and disability and quality of life).

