**Feasibility outcomes**

The feasibility outcomes include:

1. Recruitment rate: % of eligible clinicians (T1) and patients who enrolled in the study (T2)
2. Retention rate: % of contacted clinicians and patients accepting to participate and report data (T3);

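### Delivery as intended is part of the protocol's definition of feasibility but has no declared outcome, and no outcome records whether treatment followed the PDDM profile

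*Protocol*

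**What the plan says.** The general objective (Objectives) is to "assess the feasibility of conducting a complete RCT to evaluate the impact of the PDDM model". The first specific objective is "To evaluate the feasibility of the PDDM to guide assessment and treatment".

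The Outcomes section describes feasibility through willingness to participate, adherence (with questionnaire response and loss to follow-up as examples), and "whether the intervention can be delivered as intended within the clinical setting". It admits some overlap with acceptability, and then states that "we decided to use specific data collection procedures for each aspect included in these constructs".

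The next section opens with "The feasibility outcomes include" and names two items: "Recruitment rate: % of eligible clinicians (T1) and patients who enrolled in the study (T2" and "Retention rate: % of contacted clinicians and patients accepting to participate and report data (T3". Neither concerns delivery.

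Other sections bear on delivery without naming it as an outcome:

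- Intervention: after the one-day workshop, "we estimate that adequate knowledge and skills will have been provided to the participating PTs". An Excel tool, still to be developed, is to hold each patient's profile across the model's domains.
- Acceptability outcomes: T3 phone interviews ask PTs whether the model helped with assessment and treatment decisions, and how much extra time it took.
- Preliminary effect outcomes and Data analysis: the percentage of patients in each model subcategory will be tabulated, the number of visits reported, and change from T2 to T3 calculated.
- Recruitment: the aim is 10-15 PTs over 3-4 months, each supplying complete data on at least five patients, for 50-75 in total. There is no formal sample size calculation.

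**The concern.** The protocol promises a procedure for each part of feasibility and supplies outcomes for two of the three. This concerns which data are collected, so an analysis plan cannot repair it later: if treatment content is not recorded by T3, it cannot be analysed.

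The gap matters more because the study has a single arm and, under Ethical considerations, the patients' care is described as continuous with usual care. Without a record of what PTs did with the profile, care guided by the model cannot be told apart from ordinary physiotherapy. Recruitment and retention could both be high among PTs who completed the paperwork and treated as before. A decision to run the RCT would then rest on an assumption that one day of training is enough, which a feasibility study is well placed to check.

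**Working it through.** **1. Definition against outcomes.**

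| Part of feasibility (Outcomes section) | Declared feasibility outcome | Related data elsewhere in the protocol |
|---|---|---|
| Willingness to participate | Recruitment rate | Recruitment targets |
| Adherence, loss to follow-up | Retention rate | None needed |
| Delivery: assessment by the model | None | Excel profile; subcategory percentages; T3 interview; extra time |
| Delivery: treatment following the profile | None | T3 interview on usefulness for treatment decisions; number of visits |

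The assessment half of delivery is recorded but not declared as an outcome. The treatment half is not recorded: a visit count says nothing about content, and the interview asks about usefulness, not about what was done.

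**2. The protocol's own figure.** 10 PTs × 5 patients = 50 and 15 × 5 = 75, so the stated 50-75 is reproduced. These are patients with complete data; the number enrolled would be at least as large.

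**3. Precision of an added patient-level delivery outcome.** The protocol gives no expected rate, so 80% is an assumption for illustration. Exact (Clopper-Pearson) 95% intervals, ignoring clustering:

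- 40/50: 66.3% to 90.0%
- 60/75: 69.2% to 88.4%

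Patients are clustered within PTs. With m = 5 per PT, the design effect is 1 + (m − 1) × ICC. The protocol gives no ICC; for an assumed 0.02 to 0.10 it is 1 + 4 × 0.02 = 1.08 to 1 + 4 × 0.10 = 1.40. The effective sample size is then:

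- 50 patients: 50/1.08 = 46.3 down to 50/1.40 = 35.7
- 75 patients: 75/1.08 = 69.4 down to 75/1.40 = 53.6

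The approximate half-width is 1.96 × √(0.8 × 0.2 × design effect / n):

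- n = 50: 11.1 points at ICC 0, 13.1 points at ICC 0.10
- n = 75: 9.1 points at ICC 0, 10.7 points at ICC 0.10

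That is enough for a useful description of delivery at patient level.

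**4. What PT-level rates could support.** Take the smallest number of successes that gives one-sided alpha of at most 0.05 (exact binomial), with assumed unacceptable and desired rates:

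| n | 60% vs 80%: successes needed, alpha, power | 70% vs 85%: successes needed, alpha, power |
|---|---|---|
| 10 PTs | 9, 0.046, 0.38 | 10, 0.028, 0.20 |
| 15 PTs | 13, 0.027, 0.40 | 14, 0.035, 0.32 |
| 50 patients | 37, 0.028, 0.89 | 41, 0.040, 0.79 |
| 75 patients | 53, 0.037, 0.98 | 60, 0.035, 0.91 |

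Patient-level powers are upper values because they ignore clustering. At PT level, 10-15 PTs cannot support a test under either pair of rates, so any cut-off there has to be descriptive.

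**The case against.** The strongest reply is that the two-item list should not be read alone. Its opening is not exhaustive, the Outcomes section concedes overlap between constructs, and feasibility, acceptability and satisfaction are jointly primary. The Background counts acceptance, barriers and facilitators as feasibility, and PTs must agree to use the model to be included.

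Much of this stands, and it rules out two readings that a reader might infer.

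- *That the first objective cannot be answered.* The T3 interviews ask about usefulness for profiling, setting treatment needs, referral and prioritising care, and about extra time. The objective is partly informed.
- *That nothing records whether profiles were completed.* The Excel tool holds them and the subcategory percentages draw on them; completeness could be counted.

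What does not stand is the step from there to delivery. Perceived usefulness is opinion, an inclusion condition is not a measurement, and an open list still names no procedure for the part that the protocol says has one.

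A reader might also take the absence of a go/no-go benchmark as the main fault. The document does not support that. It is an omission that an analysis plan not shown here may fill, and the Recruitment section does give numerical targets, although no decision is tied to them. Nor do wide intervals measure the problem: 8 of 10 PTs gives 44.4% to 97.5% whether or not a benchmark exists.

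Finally, delivery data would not allow the change scores to be attributed to the model. A single-arm study cannot do that.

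**Conclusion.** The point holds as a mismatch within the protocol. One of the three parts of its own definition of feasibility has no declared outcome. Within that part, assessment is recorded but not counted as an outcome, and treatment is not recorded. The first objective is informed only in part, by clinicians' self-report filed under acceptability. No stated number is wrong, and the size of the gap cannot be expressed as a bias.

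This rests on the protocol text alone and on reading the promise of a procedure for each aspect as covering delivery. The precision and power figures rest on assumed rates and ICCs; they show only what the planned numbers could support. The change is cheap and worth making before enrolment. Progression cut-offs are a secondary, optional matter.

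**What to change.** Add two outcomes to the Feasibility outcomes section, each covering all enrolled patients:

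- (a) the percentage of patients with all five PDDM domains scored in the Excel tool at T2;
- (b) the percentage of flagged domains for which the PT records at least one action addressing that domain by T3, using one added field per domain, with *action* defined in the tool.

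For (b), count a flagged domain with no T3 entry as no action, and read (b) beside (a), since a patient without a profile contributes no flagged domains. Report both overall and by PT, with confidence intervals that allow for clustering within PTs.

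The cost is a short protocol edit, a few fields in a tool still to be built, and a little extra recording by PTs. The limitation is that (b) is self-reported.

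Optional: if progression cut-offs are added, take them from the Recruitment section: at least 10 PTs and at least 50 patients with complete T2 and T3 data within 4 months. A rule of 50 enrolled with, say, 80% followed up would accept 50 × 0.80 = 40 complete patients, below that target. Treat PT-level cut-offs as descriptive. Amend the retention rate so that its denominator is enrolled rather than contacted participants; otherwise people who decline at the outset count as not retained.

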**Feasibility outcomes**

The feasibility outcomes include:

1. Recruitment rate: % of eligible clinicians (T1) and patients who enrolled in the study (T2)
2. Retention rate: % of contacted clinicians and patients accepting to participate and report data (T3);

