**Recruitment**

A convenience sampling method will be used to recruit the clinicians. PTs from the two sites that express interest in participating in the study will be enrolled if they meet the inclusion criteria. An email containing all the relevant and necessary details to participate in the study including the participant’s (PTs) implication and the research team coordinates will be sent to all the clinicians from both sites (see [Appendix A](#_Annex_A:_invitation)). Patients participating in the study will be recruited based on the participating clinicians’ caseload. Each PT will have to recruit participants (new patients) by explaining in detail the purposes, process and implications of participating in the study. A formal consent form with all the aforementioned details will be provided by the PT to the patient. As this is a feasibility trial, no formal sample size calculation was conducted [17]. Instead, we aim to recruit between 10-15 PTs in order to effectively measure the feasibility of implementation of the intervention in a 3-4 months timeframe. We aim to have each PT provide complete data for at least five of their patients with non-specific LBP for an expected total of 50-75 patients.

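### The retention rate is divided by everyone contacted, not everyone enrolled, so it combines uptake with retention and does not measure loss to follow-up

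*Protocol*

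**What the plan says.** In the Protocol, section Outcomes, feasibility belongs to the primary set: "The primary outcomes measures will assess feasibility of implementation", together with clinician acceptability and patient satisfaction. The same section describes what feasibility covers and names two components separately. One is "willingness of individuals to participate in the study". The other is "the adherence/compliance of participants to the intervention (ex : response rate to questionnaire, loss to follow up").

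The section Feasibility outcomes then lists two rates:

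- Item 1: "Recruitment rate: % of eligible clinicians (T1) and patients who enrolled in the study (T2").
- Item 2: "Retention rate: % of contacted clinicians and patients accepting to participate and report data (T3").

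Item 2 is the only definition of retention in the protocol. No other section defines loss to follow-up among those enrolled.

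On who is contacted, the section Recruitment says that the invitation e-mail "will be sent to all the clinicians from both sites". Enrolment is narrower: a clinician must express interest and meet the inclusion criteria. Patients are approached by their physiotherapist. The protocol does not say how many clinicians or patients will be contacted, or what share is expected to enrol or to drop out.

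**The concern.** Retention asks what share of the people who entered the study were still providing data at the end. Its natural base is the number enrolled. Item 2 uses the number contacted, and its numerator requires both agreeing to take part and reporting at T3. A clinician who ignores the invitation is then counted in the same way as one who attended the workshop and later stopped sending data.

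This also departs from the protocol's own description of feasibility, which keeps willingness to participate apart from loss to follow-up. Item 1 covers willingness. Item 2 is where loss to follow-up should appear, but it brings willingness back in. As defined, neither rate isolates loss among the enrolled.

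What is at stake is the interpretation of a primary feasibility outcome in a study whose general objective is to judge whether a full RCT can be run. Low uptake and poor follow-up call for different remedies, and a single figure that combines them cannot show which one occurred.

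**Working it through.** **The plan's own figure.** The only related number in the protocol is the patient target. With 10-15 physiotherapists and five patients each, 10 × 5 = 50 and 15 × 5 = 75, which reproduces the stated 50-75. The present point does not depend on it.

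**Notation.** Let C be the number contacted, E the number enrolled and R the number reporting data at T3.

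- Retention as written = R/C.
- Retention among the enrolled = R/E.
- Uptake = E/C.

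Hence R/C = (E/C) × (R/E). The rate as written equals retention only if E = C, that is, if everyone contacted enrols. Otherwise it is too low. The error never goes the other way.

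**Fixed follow-up, varying contact (assumed counts).** Take 60 enrolled and 48 reporting at T3, so R/E = 48/60 = 80% throughout.

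| Contacted | Uptake E/C | As written R/C | Among enrolled R/E |
|---|---|---|---|
| 60 | 100% | 48/60 = 80% | 80% |
| 75 | 80% | 48/75 = 64% | 80% |
| 100 | 60% | 48/100 = 48% | 80% |
| 120 | 50% | 48/120 = 40% | 80% |
| 200 | 30% | 48/200 = 24% | 80% |

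Follow-up is identical in every row. Only the breadth of the invitation changes, yet the reported retention runs from 80% down to 24%.

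**Size over a range of assumptions.** At 80% retention among the enrolled:

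- uptake 30%: 0.30 × 0.80 = 24%
- uptake 50%: 0.50 × 0.80 = 40%
- uptake 70%: 0.70 × 0.80 = 56%
- uptake 90%: 0.90 × 0.80 = 72%

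Allowing retention among the enrolled of 70-90% and uptake of 30-90%, the rate as written runs from 0.30 × 0.70 = 21% to 0.90 × 0.90 = 81%.

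**Conditional consequence for a later RCT.** Suppose a planner took 1 minus this rate as drop-out and wanted 100 completers. The number to enrol would be 100 divided by the rate as written: 100/0.24 = 417, 100/0.40 = 250, 100/0.56 = 179 and 100/0.72 = 139 for the four uptake values. With retention among the enrolled it would be 100/0.80 = 125.

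**The case against.** **The information is not lost.** The number enrolled is the numerator of item 1, enrolment is marked by a consent form for both groups (Ethical considerations), and patient data are collected at T2 and T3. Anyone holding those counts can compute R/E. This stands, and it is why the repair is cheap and why the point is not a critical one. It does not make the stated definition right: the protocol fixes the denominator itself, so this is not a detail left to a statistical analysis plan.

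**Contacted might mean contacted at T3.** On that reading the base would be people already in the study. The wording is against it, because the same phrase counts those who accept to participate, which is the enrolment decision.

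**The consequences could be overdrawn.** A reader might infer that this rate will set the drop-out allowance of the RCT, or that a well-followed study would be declared a failure. The protocol supports neither. It states no such use and no success threshold, and the section Data analysis foresees only descriptive statistics and qualitative reporting for feasibility.

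**Recruitment multiplied by retention.** A reader might describe item 2 as the product of the protocol's recruitment rate and true retention. That is exact only if contacted equals eligible. Item 1 is based on eligible persons. For clinicians, the e-mail goes out before interest and eligibility are established, so the two bases need not agree. The accurate factor is enrolled/contacted.

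**The patient target.** A reader might also infer that 50-75 assumes no loss. The Recruitment section aims to have "each PT provide complete data for at least five of their patients with non-specific LBP for an expected total of 50-75 patients". This is a target for patients with complete data, with five as a minimum and no cap on enrolment. A physiotherapist may enrol more than five to reach it, so patient loss does not contradict it.

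**Conclusion.** The point holds as a definitional error in one of the two listed feasibility rates. As written, the retention rate is uptake times retention among the enrolled. It understates retention whenever anyone contacted does not enrol, and it does not capture the loss to follow-up that the protocol names as a separate element of feasibility. For clinicians, uptake below 100% is likely because of how invitations are sent. For patients it depends on how many of those approached agree, which the protocol does not predict.

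The size cannot be fixed from the document. With an assumed 80% retention among the enrolled, the understatement is 8 percentage points at 90% uptake (72% against 80%) and 56 points at 30% uptake (24% against 80%). It disappears at 100% uptake. The RCT enrolment figures apply only if a later planner reads 1 minus this rate as drop-out.

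This should be fixed, but it does not threaten the conduct of the study: the analysis is descriptive, no decision rule is tied to the rate, and the correct quantity can be computed from counts already planned.

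**What to change.** Replace item 2 under Feasibility outcomes with a definition on the enrolled base: retention rate = participants with T3 data divided by participants enrolled. Report it separately for physiotherapists (enrolled = consented at the workshop) and for patients (enrolled = consented at T2). Report enrolled divided by contacted on its own, labelled uptake, again by group.

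Leave the target of 50-75 patients with complete data as it is.

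The cost is one sentence. The consent forms and the T2 and T3 records already supply the enrolled and reporting counts, and the present definition already requires the number contacted, so no new data collection is needed.

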**Acceptability outcomes**

The clinician’s acceptability outcomes will be assessed via questionnaires and semi-structured phone interviews and include:

1. Clinician’s perception of suitability of the assessment procedures to refine the diagnosis label will be assessed at T3 via a brief phone interview: During your assessment with this patient, was the PDDM useful to:
   1. Establish a complete clinical profile of your patient?
   2. Reduce diagnostic uncertainty?
   3. Identify all the factors driving pain and disability to refine your clinical diagnosis?
2. Clinician’s perception of suitability of the assessment procedures to target adequate treatment will be assessed at T3 via a brief phone interview: After your assessment, was the PDDM useful to improve decisions points related to:
   1. Establish the specific treatment needs of your patient (target care)?
   2. Refer out to other health care providers if indicated (interdisciplinary collaboration)?
   3. Prioritize care (importance and timing)?
3. Clinician’s attitudes and beliefs concerning the management of pain will be assessed before and after the training and at the end of the data collection period (T0, T1 and T3) via a self-administered questionnaire, the *Pain Attitudes and Beliefs Scale for Physiotherapists* (PBS-PT) [20] in order to explore the effect of the training on this variable ;
4. Clinician’s appreciation of clinical training (assessed within a week after the training, T1) and appreciation of the web-based support (assessed at T3) will be measured via phone interviews to collect their opinion on the strengths, limitations and suggestions on how to improve the quality of the various content elements of the training via open-ended questions (see [Appendix C](#_Annex_C_–)).
5. Additional time required to complete assessment and guide treatment (T3);
   1. Compared to a routine assessement, how much extra time do you need to perform an assessment based on the tenants of the PDDM model?

